### Variables and Data Collection

Collected data consisted of demographic data, medical history reviews, previous radiotherapy histories, history of surgery and treatment for AK, definition of AK lesions (localization, number, grade, and photographs), and assessments of the subjects’ skin aspects.

For women of childbearing age, a urine pregnancy test was performed at screening or before the beginning of the treatment.

Several scales (pain, aesthetic aspect, and treatment tolerance) and questionnaires (DLQI and satisfaction) were used.

**Figure 5 figure5:**
[figure not shown]
Illustration of the classical photodynamic therapy treatment procedure.

**Figure 6 figure6:**
[figure not shown]
Illustration of the new photodynamic therapy treatment procedure.

### Data Management

All medical observations were maintained in the patient’s file; the data to be analyzed in the study were reported on an electronic case report form according to Good Clinical Practices and the sponsor’s standard operating procedures. The data collection procedure was exhaustive and verified regularly by a clinical research associate according to the protocol. Any deviation from the protocol was noted, and the reason for the deviation was documented. Discrepancies in the data were brought to the attention of the clinical team and investigational site personnel in the form of a query. Resolutions to these issues are reflected in the database.

### Statistical Methods

Continuous variables will be reported as means and standard deviations, and categorical variables will be reported as frequencies and percentages. The Shapiro-Wilk test will be used to assess the normality of the distribution. This normality will also be evaluated graphically.

#### Analysis of Primary Objective

In this study, each patient could have several lesions. We considered the “patient” effect. Indeed, a correlation could exist between the outcome measures in a single patient (cluster effect). The complete response rate of lesions will be analyzed according to the treatment groups (N-PDT or C-PDT) using the generalized linear mixed model to consider the cluster effect with an adjustment for the period (by the area). The 95% confidence interval of the absolute difference in response rates between the two groups will be calculated (D=N-PDT – C-PDT). We will conclude noninferiority if the lower limit of this 95% confidence interval is greater than 10%. If noninferiority is confirmed, a superiority test will be performed.

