### Sample Size

The study is designed to have a statistical power of 80% with a one-sided alpha level of .025 to determine noninferiority in terms of a complete lesion response rate 3 months after N-PDT compared with C-PDT. Assuming a complete lesion response rate of 75% in both areas, an intrapatient correlation in both lesions and areas, and a noninferiority margin of 10%, the number of required lesions per area is 245. This value corresponds to 42 patients, assuming 12 lesions per patient (6 lesions per patient per area).

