#### Initial Visit: Preparation and Treatment of Lesions

##### Selection of Treatment Areas

Each subject’s skin aspect was evaluated, and the two areas were treated according to the study protocol and randomization design. Randomization was performed after the definition of the axis of symmetry to avoid selection errors (Figure 4).

The global area of the scalp and front of the face was divided into two symmetrical areas (area A and area B) containing the same number and same grades of AK lesions. The areas to be treated were localized between the eyebrows and the neck. Included AK lesions were located, counted, graded, and photographed.

For each patient, *n* lesions in area A were treated with one technique (N-PDT or C-PDT) and *n* lesions in area B were treated with the other technique (C-PDT or N-PDT) (5≤*n*≤7).

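### The primary model names only the patient as cluster, so the noninferiority interval may be too narrow if lesions in the same treated area respond alike

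*Protocol article*

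**What the plan says.** Analysis of Primary Objective explains that a patient contributes several lesions and that "a correlation could exist between the outcome measures in a single patient (cluster effect"). Lesion response is then compared between techniques with a generalized linear mixed model that takes this cluster effect into account. The model also has an adjustment for period, with the area given in brackets. The noninferiority decision uses the lower limit of the 95% confidence interval for the absolute difference D (N-PDT minus C-PDT).

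Selection of Treatment Areas shows what is allocated. Within a patient, "lesions in area A were treated with one technique (N-PDT or C-PDT") and the same number in area B with the other, with 5 to 7 lesions per area.

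Sample Size sets a "statistical power of 80% with a one-sided alpha level of .025" and names two levels of dependence: "an intrapatient correlation in both lesions and areas". It concludes that "the number of required lesions per area is 245" and adds: "This value corresponds to 42 patients, assuming 12 lesions per patient (6 lesions per patient per area"). No correlation value is given.

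**The concern.** The area within the patient is the unit that receives a technique. Its lesions share one dressing, one illumination and the same region of skin. The article itself gives a reason why delivery may vary from one patient's area to another: the Introduction says rigid planar sources do not light convex surfaces evenly, so the dose actually delivered in C-PDT is unknown.

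A random intercept for the patient alone makes two lesions in the same area exactly as correlated as two lesions in opposite areas. Any further variation belonging to one patient's area enters the true variance of D but not the model's standard error. The lesions of an area then count as more independent evidence than they are. The decision rests on one limit of the interval, so an interval that is too short raises the chance of declaring an inferior device noninferior.

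The sample size text names the area level. The analysis text does not carry it over as a cluster.

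**Working it through.** **Inputs.** From Sample Size: response 75% in both areas, margin 10 points, one-sided alpha .025, power 80%, m = 6 lesions per area, 245 lesions per area, 42 patients. The within-area ICC (rw) and between-area ICC (rb) are not given and are assumed below. The noninferiority limit is taken as D = −10 points.

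**The plan's own figure.** With independent lesions, n per area = 2 × 0.75 × 0.25 × (1.960 + 0.842)² / 0.10² = 294.3, so 295. The stated 245 is lower by a factor 245 / 294.3 = 0.832. In a split-area design with m lesions per area, the variance factor for D is

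F(true) = 1 + (m − 1)rw − m·rb.

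With equal ICCs this reduces to 1 − r, and 0.832 gives r = 0.168. Many unequal pairs also give 0.832, so 245 can be neither confirmed nor refuted. Patients: 245 / 6 = 40.8, so 41, close to the stated 42.

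**What a patient-only model assumes.** It fits one correlation, roughly the average over the other 11 lesions of the patient (5 in the same area, 6 in the opposite one):

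F(model) ≈ 1 − [(m − 1)rw + m·rb] / (2m − 1).

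The true standard error is √(F(true) / F(model)) times the model's, and the actual one-sided error is 1 − Φ(1.96 / ratio).

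**Example, rw = 0.218, rb = 0.168.** F(true) = 1 + 1.090 − 1.008 = 1.082. F(model) = 1 − 2.098 / 11 = 0.809. Ratio = √(1.082 / 0.809) = 1.156. Error = 1 − Φ(1.96 / 1.156) = 4.5%.

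| rw | rb | F(true) | F(model) | SE ratio | One-sided error | Lesions per area needed |
|---|---|---|---|---|---|---|
| 0.168 | 0.168 | 0.832 | 0.832 | 1.00 | 2.5% | 245 |
| 0.20 | 0.195 | 0.832 | 0.803 | 1.02 | 2.7% | 245 |
| 0.25 | 0.236 | 0.832 | 0.757 | 1.05 | 3.1% | 245 |
| 0.30 | 0.278 | 0.832 | 0.712 | 1.08 | 3.5% | 245 |
| 0.188 | 0.168 | 0.932 | 0.823 | 1.06 | 3.3% | 275 |
| 0.218 | 0.168 | 1.082 | 0.809 | 1.16 | 4.5% | 319 |
| 0.268 | 0.168 | 1.332 | 0.787 | 1.30 | 6.6% | 393 |

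In rows 2 to 4, rb is chosen so that F(true) stays at the 0.832 implied by the plan. In the last three rows rb is fixed at 0.168 and rw exceeds it by 0.02, 0.05 and 0.10. Coverage of the 95% interval in those three rows is 93.4%, 91.0% and 86.8%.

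**Simulation.** 42 patients, 6 lesions per area, true rates 75% and 65%, patient SD 0.9 on the logit scale, 1000 runs per setting. The Monte Carlo standard error at 2.5% is √(0.025 × 0.975 / 1000) = 0.5 points.

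| Patient-by-area SD | Error, patient-only model | Error, per-patient differences | Width of per-patient interval |
|---|---|---|---|
| 0 | 2.6% | 3.1% | 0.153 |
| 0.5 | 4.6% | 3.1% | 0.170 |
| 0.8 | 5.7% | 2.1% | 0.190 |
| 1.0 | 7.8% | 1.5% | 0.204 |

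The patient-only interval stayed at a width of about 0.15 in all four settings, so it did not respond to area-level variation.

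**The case against.** The best defence is that this is a journal article. Random-effect levels are often left to the analysis plan, the model sentence does mention area, and the sample size shows that the authors knew of the area level. An area term may exist in a document not shown. This stands as a caution, but it does not remove the point. The article is not silent: it names the patient as the cluster and defines the cluster effect as correlation within a patient. The adjustment for period and area is unclear. In its ordinary reading it is a fixed effect common to all patients, which removes an average difference between areas and not the deviation of one patient's area.

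A second defence is that the areas are chosen to be symmetrical, with the same number and grades of lesions. This limits baseline differences between areas. It does not limit differences that arise from the treatment session.

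A reader might infer that the interval simply is too narrow. The documents do not support that: it requires rw to exceed rb, and neither value is given. A reader might also take the larger error rates as typical. The pairs behind 3.3% to 6.6% need 275 to 393 lesions per area, more than the planned 245. With F(true) held at 0.832, an error near 6% would need a within-area ICC of about 0.5. True correlations may differ from those planned, so the larger figures remain possible, but they do not follow from the plan.

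Finally, a reader might suspect that a logit model read at a random effect of zero would distort the absolute difference. The article does not say that D is obtained that way. At a true deficit, such a reading would overstate it and work against N-PDT, so it adds nothing to this concern.

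**Conclusion.** The point holds in conditional form. As written, the primary analysis clusters on the patient only, while treatment is assigned by area and the sample size assumes correlation at area level too. The interval is right if lesions in the same area are no more alike than lesions in opposite areas, and too narrow in favour of N-PDT if they are more alike. The inflation is small for the ICC pairs above that agree with the planned 245 lesions and moderate if area-level correlation is stronger than planned. All the error rates rest on assumed ICCs, 6 lesions per area, the patient-only reading of the model and a limit of −10 points. The table uses a large-sample approximation.

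**What to change.** Add a random effect for area within patient (patient by area) to the primary mixed model and keep the prespecified area adjustment. Take the marginal absolute difference with its 95% confidence interval from this model for the noninferiority decision. As a check, report the per-patient difference in proportion of lesions cleared (N-PDT area minus C-PDT area), adjusted for area, with a t-based interval. State the two ICCs behind 245, so that the planning and analysis assumptions can be compared.

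The change needs new wording and one altered model, and no new data. Because the article reports that the data were analysed at the end of 2018, in practice this may mean a re-run. The price is a somewhat wider interval if area-level correlation is present. In the simulation the per-patient interval, unadjusted for area, was 0.153 wide without such correlation, against about 0.15 for the patient-only model, and 0.170 to 0.204 with it. An interval that counts this correlation also exposes lower power: with 42 patients (42 × 6 = 252 lesions per area) and rb = 0.168, about 77%, 70% and 61% when rw is higher by 0.02, 0.05 and 0.10.

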## Methods

### Trial Design

The trial was a proof-of-concept study and was a comparative (split-face and intraindividual comparison), randomized, open-label, single-center evaluation of the noninferiority of N-PDT compared with C-PDT.

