**Figure 4 figure4:**
[figure not shown]
Schematic of the randomization process for area A and area B. C-PDT: Aktilite CL 128 device; N-PDT: Flexitheralight device.

Before applying MAL, the areas were prepared by removing the crusts with a small curette and gently scraping the surface of the lesions to roughen the surface.

Pain in the two treated areas was scored by the patient after treatment: first for the N-PDT area and then for the C-PDT area.

Patients complete a quality of life questionnaire (Dermatology Life Quality Index [DLQI]) and a satisfaction questionnaire at the end of the procedure.

The total duration of the treatment procedure (treatment of areas A and B) was approximately 3 hours and 20 minutes.

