##### Area A: Classical Photodynamic Therapy

MAL was applied (approximately 1 mm thick) with a spatula on the selected lesions and over an area of 5 to 10 mm of normal skin surrounding the lesions. The treated area was covered with an occlusive (Tegaderm, 3M) and light-proof (aluminium foil) dressing for 3 hours. Afterward, the dressing was removed, the area was cleaned with a saline solution, and the skin was then immediately exposed to a continuous red light spectrum delivered by an Aktilite CL 128 device (Galderma Laboratories) (570 to 670 nm) for 10 minutes for a total light dose of 37 J/cm^2^ (Figure 5).

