##### Area B: New Photodynamic Therapy

MAL was applied as described for the area A treatment, and the area was covered with an occlusive and transparent dressing (Tegaderm, 3M) for 30 minutes whereas both a transparent occlusive dressing and a light-proof dressing (aluminium foil) was applied over the area randomized to receive C-PDT. Afterward, the dressing was retained, and irradiation was applied with the Flexitheralight device (635 nm) for 2 hours and 30 minutes. A total light dose of 37 J/cm^2^ was administered (Figure 6). After the end of the illumination, area B was protected with aluminium foil.

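### The primary model adjusts for a "period" that a single-session split-face design does not have; the usable factor, area A/B, is labelled in two conflicting ways, and lesion grade could be added at almost no cost

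*Protocol article*

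**What the plan says.** Under Analysis of Primary Objective, the complete response of lesions is analysed with a generalised linear mixed model that allows for clustering within patient, "with an adjustment for the period (by the area"). No other adjustment is named, and the term is not defined.

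Trial Design describes a "comparative (split-face and intraindividual comparison), randomized, open-label, single-center evaluation of the noninferiority of N-PDT compared with C-PDT". The text below Figure 4 gives one procedure for both areas: "The total duration of the treatment procedure (treatment of areas A and B) was approximately 3 hours and 20 minutes".

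Area is described in two ways:

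- Under Selection of Treatment Areas, the n "lesions in area A were treated with one technique (N-PDT or C-PDT") and the n lesions in area B with the other. Randomisation follows the definition of the axis of symmetry.
- The procedure subsections are headed "Area A: Classical Photodynamic Therapy" and "Area B: New Photodynamic Therapy". The body text of the second also uses area B to mean the N-PDT area when it describes protecting the skin after illumination.

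On grade, Selection of Treatment Areas requires two areas "containing the same number and same grades of AK lesions", and the included lesions are graded at the initial visit.

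**The concern.** Period is a crossover term. In a crossover each patient receives the treatments at different times, in an order set by randomisation, and the model removes any time effect. Here there is no second occasion in the primary comparison. A programmer therefore has to guess what the variable is, and the guesses differ in consequence: some leave treatment estimable and some do not.

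The model produces the confidence interval on which noninferiority is judged. The trial is open-label, the plan says the data will be analysed without blinding, and recruitment closed at 27 of the planned 42 patients. An undefined term in the primary model leaves room for choice after the data are seen.

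Grade is a smaller matter. When a design matches on a factor that predicts outcome, a model that omits the factor does not credit the matching in its standard error. With 27 patients, precision is scarce.

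**Working it through.** **1. Is there a period in time?** The inputs are the two procedure subsections and the text below Figure 4.

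- N-PDT: 30 min of occlusion + 150 min of illumination = 180 min.
- C-PDT: 180 min of occlusion, then 10 min of illumination = 190 min.
- Stated total for both areas: 3 h 20 min = 200 min. Treating the areas one after the other would take 180 + 190 = 370 min, so they run together.

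It is one session. Within it, N-PDT illumination ends at about the time C-PDT illumination begins, in every patient. Time order is therefore a function of technique and is not randomised.

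**2. Which codings leave treatment estimable?** The fixed effects are an intercept, treatment T (1 = N-PDT) and the adjustment factor F. Treatment can be separated from F only if the matrix [1, T, F] has rank 3. It was checked for 42 patients, 2 areas and 6 lesions per area, with 1:1 allocation in blocks of 6.

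| Reading of F | Relation to T | Correlation | Rank |
|---|---|---|---|
| Common session | F constant | undefined | 2 |
| Time order of illumination | F = 1 − T | −1 | 2 |
| Area, as the procedure subsections label it | F = T | 1 | 2 |
| Area A/B, as randomised | balanced against T | 0 | 3 |

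In the last row, 21 patients have N-PDT on area A and 21 on area B, so each area-by-treatment cell holds 21 × 6 = 126 lesions. With a patients one way and b the other, the correlation has size |a − b|/(a + b). If 27 patients filled the blocks in sequence, the worst split is 15 to 12, giving 3/27 = 0.11. The rank is still 3.

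**3. Does leaving out grade matter?** When grade is the same in both areas of each patient, adding it to a linear within-patient analysis leaves the estimated difference unchanged. In 4,000 simulated trials of 42 patients, the SD of the estimate was 0.0350 with and without grade. An unadjusted interval from patient-level differences covered 95.4%. Omission therefore causes no bias.

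What can change is the model-based standard error. For clearance p1 in grade I, p2 in grade II, a share w of grade I and overall clearance p, grade explains w(1 − w)(p1 − p2)²/[p(1 − p)] of the lesion-level variance. The clearance rates are assumptions, because the article gives none by grade.

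- 85/60%, w = 0.5: 0.25 × 0.0625/0.1994 = 0.078
- 85/60%, w = 0.6: 0.24 × 0.0625/0.1875 = 0.080
- 80/70%, w = 0.5: 0.25 × 0.01/0.1875 = 0.013

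If all of this variance lies within patients, the interval is too wide by a factor of 1/√(1 − share): 1/√0.92 = 1.043 at the top and 1/√0.987 = 1.007 at the bottom.

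**4. What is that in power?** The plan's figure of 245 lesions per area can be reached but not verified. Independent lesions need 2 × 0.1875 × (1.960 + 0.842)²/0.10² = 294.3, or 295. A common intrapatient correlation of about 0.168 gives 294.3 × 0.832 = 245, but the article states no value. I therefore take 80% power at 42 patients as given.

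- 27 patients, no grade: Φ(2.802 × √(27/42) − 1.96) = 0.613
- 27 patients, effective number divided by 0.92: 0.649

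This gain of 3.6 points is an upper end, because it treats all grade variance as recoverable. Simulations of 27 patients with 6 lesions per area, using linear models with patient effects, gave less:

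- 85/60%, grades mixed within patients: power rose from 56.5% to 59.2%.
- 80/70%, grades mixed within patients: power rose from 58.4% to 59.0%.
- Grade varying only between patients: no change.

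**The case against.** The strongest reply is that the parenthesis already answers the question: area plays the role that period plays in a crossover. Selection of Treatment Areas says that either technique may fall on area A, and randomisation comes after the axis is set. The N-PDT procedure text itself refers to the area randomised to C-PDT. If A always meant C-PDT, the randomisation would have no content. This stands. A reader might infer from the procedure headings that the primary model cannot be fitted. The documents do not support that: those headings describe how each technique is delivered and do not define a model variable.

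The second reply is that covariate choice is often left to an analysis plan, that the article is condensed, and that matching already balances grade. This also stands, in that omitting grade is not an error. A reader might infer bias from the omission, or a dependable rise in power from 61% to 65%. Neither follows. The estimate does not move, and those power figures rest on assumed clearance rates at the favourable end. An analysis of patient-level differences has a similarly small standard error without using grade.

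Third, the article says data analysis was performed at the end of 2018, so a covariate added now is post hoc in an open-label trial. This is correct, and the fix allows for it.

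What the replies do not remove is that the term is undefined, that its first word has no referent in this design, and that the labels for its second word contradict each other.

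**Conclusion.** The point holds as a repair of wording, with a small optional gain in precision. A period in time is constant or aliased with treatment. Area as randomised is a sound adjustment and fully estimable. Aliasing arises only if the A = C-PDT, B = N-PDT labels are carried into the data.

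Grade is an improvement and its omission is not a fault. Without it, coverage stays near 95% and the model-based interval is about 1 to 5% too wide when grades mix within patients. That is worth about 0.5 to 4 points of power at 27 patients, and nothing if each patient's lesions share one grade. These sizes rest on assumed clearance of 80/70% to 85/60% and on linear models. In a logistic model, grade would shift the conditional odds ratio, but not the marginal absolute difference that the plan reports.

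**What to change.** - Under Analysis of Primary Objective, replace the period term with area (A/B, as labelled before the envelope is opened). A/B is safer than left/right, because the investigator sets the axis from the distribution of lesions.
- Retitle the two procedure subsections as C-PDT area and N-PDT area, and correct the reference to area B in the N-PDT text, so that the letters keep their randomised meaning.
- Add lesion grade at visit 1 (I or II) as a lesion-level fixed covariate, and standardise the absolute difference over the observed grades.

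The cost is wording and one covariate that is already collected. If the primary analysis has been run, state which coding of area was used, keep the planned result as primary, and report the grade-adjusted interval beside it as a labelled post hoc analysis.

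### The noninferiority rule has the wrong sign: it requires the lower limit of N-PDT minus C-PDT to exceed +10%, so an equivalent device would almost never pass

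*Protocol article*

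**What the plan says.** Three consecutive statements in the protocol article's Analysis of Primary Objective set the decision rule:

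- The direction of the difference: "The 95% confidence interval of the absolute difference in response rates between the two groups will be calculated (D=N-PDT – C-PDT"), that is, new device minus classical device. The endpoint is complete response of lesions, so a positive D favours N-PDT.
- The criterion: "We will conclude noninferiority if the lower limit of this 95% confidence interval is greater than 10" percent. No minus sign is printed.
- The next step: "If noninferiority is confirmed, a superiority test will be performed".

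The Sample Size section describes what the trial was built to show: "The study is designed to have a statistical power of 80% with a one-sided alpha level of .025 to determine noninferiority". Its inputs are "Assuming a complete lesion response rate of 75% in both areas" and "a noninferiority margin of 10" percent. It also refers to "an intrapatient correlation in both lesions and areas" but gives no value. The result is 245 lesions per area, or 42 patients with 6 lesions per area.

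Trial Design and Discussion both give the aim as showing that N-PDT is not inferior to C-PDT. Nowhere does the article state a limit of −10%.

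**The concern.** For a success rate with D taken as new minus control, noninferiority with a margin of 10 points means ruling out that the new device is worse by 10 points or more. The lower confidence limit must therefore lie above −10%. A lower limit above +10% shows instead that the new device is better by more than 10 points. That is a different hypothesis and a far harder one.

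The printed rule would not raise the rate of false positive claims. Applied literally, it would make a trial that assumes equal response rates fail almost with certainty. In practice someone would reinterpret it. The study is open-label, efficacy is assessed by investigators who know the allocation, and the analysis is unblinded (Implementation and Blinding). The criterion for the primary conclusion should not need silent correction after the data have been seen.

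**Working it through.** **Inputs.** From Sample Size: response 75% in both areas (true D = 0), margin 10 points, one-sided alpha 0.025, power 80%, 245 lesions per area, 6 lesions per patient per area. From Analysis of Primary Objective: D = N-PDT − C-PDT, two-sided 95% interval, limit printed as +10%. From Results: 27 patients recruited instead of 42.

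**Step 1. The plan's own sample size.** With independent lesions,

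n = 2 × 0.75 × 0.25 × (1.960 + 0.842)² / 0.10² = 294.3, rounded up to 295 per area.

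The article states 245, which needs a variance factor of 245 / 294.3 = 0.832. With 6 lesions per area the factor is 1 + 5ρ(within area) − 6ρ(between areas). A common correlation of 0.168 gives 0.832, and so do other pairs. Since no correlation is printed, 245 can be neither confirmed nor refuted. The sign question does not depend on it. Both standard errors are carried forward as assumptions:

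- implied by the stated power: SE = 0.10 / (1.960 + 0.842) = 0.0357;
- independent lesions: SE = √(0.375 / 245) = 0.0391.

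**Step 2. Probability of passing a limit c.** By the normal approximation,

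P(lower limit > c) = Φ((D − c)/SE − 1.96).

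| At true D = 0, 245 lesions per area | SE 0.0357 | SE 0.0391 |
|---|---|---|
| Printed rule, c = +0.10 | Φ(−4.76) = 9.6 × 10⁻⁷ | 3.2 × 10⁻⁶ |
| Rule with c = −0.10 | 80.0% | 72.4% |
| Observed D needed, printed rule | above +17.0 points | above +17.7 points |
| Observed D needed, c = −0.10 | above −3.0 points | above −2.3 points |

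The 80.0% matches the plan by construction, because that SE was solved from the stated power.

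**Step 3. What the printed rule demands.** At a true D of +10 points, (D − c)/SE is zero and the probability is Φ(−1.96) = 2.5%, whatever the SE. Below +10 points it is smaller still, so no value of the undisclosed correlation rescues the rule at D = 0.

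For 80% probability with the SE held at 0.0357, D must be 0.10 + 2.80 × 0.0357 = 0.20. The binomial variance shrinks at high response rates. Allowing for that, with C-PDT at 75%, the required D is 18.2 points (SE implied by the stated power) or 18.9 points (independent lesions). That is an N-PDT response of about 93% to 94%.

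**Step 4. At the size reached.** Assuming 6 lesions per area, 27 patients give 162 lesions per area. The two standard errors become 0.0439 and 0.0481, and the printed rule passes at D = 0 with probability 1.1 × 10⁻⁵ to 2.7 × 10⁻⁵.

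**Step 5. The follow-on test.** Superiority needs a lower limit above 0. A lower limit above +10% already satisfies that, so under the printed rule the superiority test can never fail once it is reached. The sequence has meaning only with −10%.

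**The case against.** The strongest reply is that this is a missing character and not a choice of analysis. The 10% margin, the equal response rates, the stated aim and the superiority step together let a reader recover −10%, and a dropped minus sign is indeed the likeliest cause. That explains the error but does not remove it: no sentence states −10%, and the faulty one is the sole decision rule for the primary conclusion.

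The minus may also have been lost when the text was read from PDF. This cannot be fully excluded, and the published page is worth checking. However, the dash in the definition of D one sentence earlier is intact, and nothing suggests lost text.

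Two further points stand as limits on the finding:

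- The article is a condensed account and the analysis plan is not shown, so there is no basis for saying that the plan, or the analysis as run, has the same error.
- The standard error is an assumption, since the correlation is not given. The result is a range of about 1 to 3 in a million at the planned size, and about 1 to 3 in 100,000 with 27 patients. Likewise, +20 points for 80% power holds only with a constant SE, and about +18 to +19 is the better figure. None of this changes the direction.

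**Conclusion.** The concern holds. As printed, the primary rule tests whether N-PDT is better by more than 10 points, contrary to the stated aim, margin and power. Under the design assumption of equal response it would be met with near-zero probability, against the 80% claimed. With −10% the probability is 72% to 80%, in line with the Sample Size section. These figures rest on the normal approximation and on the two assumed standard errors. That the printed rule cannot exceed 2.5% for any true difference up to +10 points depends on neither SE, only on the normal approximation. The point must be fixed because it governs the main conclusion of the trial. Whether 245 lesions can be reproduced is a separate matter.

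**What to change.** Replace the criterion with: noninferiority will be concluded if the lower limit of the two-sided 95% confidence interval of D (N-PDT minus C-PDT) is greater than −10 percentage points; superiority will then be concluded if that lower limit is greater than 0.

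The cost is one corrected sentence in the protocol article. The article reports that the data analysis was performed at the end of 2018, so the sponsor should also check the full protocol and analysis plan for the same wording, and state in the results report that −10 points was the prespecified limit and the one applied. No change to the design, the data or the model is needed.
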